## 1 Study instructions

- 1. **Backgrounds**

The excimer laser served as a surgical tool was first introduced into ophthalmology and refractive surgery almost 30 years ago. Compared with photorefractive keratectomy (PRK), laser situ keratomileusis (LASIK）reduce postoperative pain, haze and accelerate visual recovery. LASIK is nowadays the most popular corneal refractive surgery around world. With the development of femtosecond laser (FEMTO), flap creation methods were improved at the same time. Sub-Bowman’s keratomileusis (SBK) combines the advantages of PRK and LASIK, creates thinner flaps in accurate and precise ways. Thus, SBK improved the efficacy, tolerability, and safety of refractive surgery.

Keratoconus is a bilateral asymmetry ectasia disease, which is characteristic with cornea thinning. However, when patients were in early stage, there were no obvious clinical signs and symptoms. Even the most sensitive corneal topography could not diagnosis. The only complain was reduced visual acuity. If the preoperative screening missed such kind of patients, cornea refractive surgery might lead to keratectasia. Thus, it is important to diagnose these subclinical patients in the stage of cornea thickness thinning.

Optical coherence tomograghy (OCT) relays on the principles of low-coherence interferometry to differentiate corneal sublayer structures. Anterior segment OCT advantaged in high acquisition speed, high axial resolution and non-invasive contact. With improved imaging technologies and surgical skills, it is promising that the diagnosis and treatment method will benefit more patients and scientific researchers.

**1.2 Aims**

A. Using OCT to obtain corneal images before LASIK, post LASIK 1 day, 1 week, 2 weeks, 1 month. Compare the differences between two flap creation methods.

B. Observe the cornea images acquired from keratoconus patients in different stages. Analysis thickness data and the relationship between the thickness and stage.

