**1.3** **Hypothesis**

During the observation of following-ups, OCT images might capture the changes before and after LASIK. The relationship between flap creation methods, ablation depth and corneal thickness might be captured. After LASIK, cornea edema might appear on the OCT images. As the longer observation time after surgery, cornea edema might reduce. Slit lamp will be used during following-ups and assist to image cornea. OCT will image the interfaces and boundaries of corneal sublayers and flaps.

At the same time, clinical exam results will be documented. Combined with OCT images, correlation between refractive regression, corneal curvature and corneal edema will be studied.

Keratoconus patients will be examed by clinical instruments. Patients of different stages will be included. OCT images will analysis combined with clinical data to study the relationship between the corneal thickness and disease courses.

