**3 Study design**

**3.1 Subjects：**recruit subjects as protocol.

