**3.3.2 Formal study**

**（1）visiting spots：**Pre, post 1 day, 1week, 2 weeks, 1month, 3months.

**（2）OCT scanning：**according torandom number table, select one eye.

**A. UL-OCT：**run: C:\OCT\combined_x-y\OCT-T34-Combined_1.vi

1.Obtain OCT images as following：

**1）Central 3D radial scanning：**calibrated scan width 18.291mm.Scanning setting：“X/Y scan width” set as 15, “line rate” set as 24000 k/A-line，“scan pattern” set as 2048×324 mm radial.

[figure not shown]

**2）Horizontal 2D scanning：**calibrated scan width 12.139 mm. Scanning setting：“X/Y scan width” set as 10, “line rate” set as 24000 k/A-line，“scan pattern” set as 2048×324 mm.

[figure not shown]

**3）Vertical 2D scanning：**calibrated scan width 12. 248 mm. Scanning setting：“X/Y scan width” set as 10, “line rate” set as 24000 k/A-line，“scan pattern” set as 2048×324 mm.

[figure not shown]

**2. Naming rules：** NO1_XX_S_1M_OD_2D_X10_1

**3. Data saving：** E:\LASIK_OCT\UL\Time\Subject

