**3.5 Post refractive surgery controls**

Flap creation methods：

1. One-Use Plus SBK Moria microkeratome (Moria, Antony, France);
2. IntraLase Femtosecond Laser (Abbott Medical Optics, Santa Ana, CA, USA).

Pre operation medication：

(1) Levofloxacin

(2) Artificial tears (one of three)

Sodium carboxymethylcellulose

Dextran hydroxypropyl methyl cellulose

Polyvinyl Alcohol

Post operation medication：

(1) Levofloxacin

(2) Artificial tears (one of three)

Sodium carboxymethylcellulose

Dextran hydroxypropyl methyl cellulose

Polyvinyl Alcohol

(3) Fluorometholone Acetate

Notice: Keep records if temporarily adjust the medication.

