**3.6 Data analysis:**

All data were collect and save in Excel to build a database.

Statistical methods were used to analysis data.

1. T-test；
2. Liner Regression, Pearson’s correlation.

4 Subjects information

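### Aim A compares two flap methods without saying how a patient comes to receive one, and section 3.6 names no adjusted analysis for it

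*Protocol*

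**What the plan says.** Section 1.2, Aim A, sets out to "Compare the differences between two flap creation methods" on OCT images taken before and after LASIK. Section 3.5, under "Flap creation methods", lists two: "One-Use Plus SBK Moria microkeratome" and "IntraLase Femtosecond Laser". It gives no rule or ratio for who receives which. Section 3.1 adds only "recruit subjects as protocol".

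The one random step is in section 3.3.2, under OCT scanning: "according torandom number table, select one eye". It concerns the eye, not the flap.

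Section 3.6 lists two analysis entries. The first is a T-test, not stated to be paired or two-sample. The second is "Liner Regression, Pearson’s correlation", with no outcome, covariate or aim. Section 1.3 does name the variables that belong together: "The relationship between flap creation methods, ablation depth and corneal thickness might be captured".

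**The concern.** How patients come to a treatment method is a matter of design and belongs in the protocol. It decides whether a difference between methods can be attributed to the method. Here the reader cannot tell whether the flap comparison is randomised, follows surgeon or patient choice, or follows calendar time.

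The gap matters because some of the outcomes depend strongly on things other than the flap. Post-operative total corneal thickness is, to a first approximation, pre-operative thickness minus ablation depth plus healing change. Section 3.2.1 admits sphere from -1.00 to -12.00 D, so ablation depth must vary widely. If the patients given one method are more myopic or have thinner corneas, an unadjusted comparison reports that difference as an effect of the flap.

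There is also a data gap. Section 1.3 needs ablation depth, but it is not among the examinations in section 2.4, the screening items in section 3.3.1 or the procedures in section 3.3.2. An analysis plan cannot adjust for a variable that was not recorded. Subjective refraction is recorded and would be a partial stand-in.

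**Working it through.** **The plan's own figure.** There is none to reproduce. The protocol states no sample size, power, SD or expected difference. Everything below is illustration on assumed inputs, except the sphere range.

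**What each relevant section fixes**
- Comparison: microkeratome against femtosecond laser (1.2, 3.5).
- Assignment to method: not stated (3.1, 3.5).
- Randomness: choice of eye only (3.3.2).
- Analysis: T-test, linear regression and correlation, none linked to an aim (3.6).
- Outcomes measured: corneal thickness (2.1); epithelium, Bowman's layer and flap (2.2).
- Pre-operative thickness: available from the pre-operative OCT visit (3.3.2) and from ultrasound pachymetry (3.3.1).
- Ablation depth: named in 1.3, not listed as collected.

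**Illustration 1: false-positive rate in standardised units.** Let r be the correlation of the covariate with the outcome, d the covariate imbalance between methods in SD units, and n the number of eyes per method. With no true method effect, the unadjusted difference is biased by r × d SD. The two-sided 5% test rejects with probability Φ(b − 1.96) + Φ(−b − 1.96), where b = r·d / √(2/n). For n = 40, √(2/40) = 0.2236:
- r = 0.5, d = 0.25: b = 0.125/0.2236 = 0.56, rate 8.6%
- r = 0.8, d = 0.25: b = 0.200/0.2236 = 0.89, rate 14.5%
- r = 0.5, d = 0.5: b = 0.250/0.2236 = 1.12, rate 20.1%
- r = 0.8, d = 0.5: b = 0.400/0.2236 = 1.79, rate 43.2%
- d = 0: rate 5% whatever r is

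**Illustration 2: micrometres, total thickness only.** Assume 10 to 16 µm of ablation per dioptre, a 1 D difference in mean correction between methods, an outcome SD of 45 µm and 30 eyes per method. The standard error is 45 × √(2/30) = 11.6 µm. Shifts of 10, 13 and 16 µm give rejection rates of 13.8%, 20.1% and 28.0%.

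**Would a T-test on change from the pre-operative scan solve it?** It removes pre-operative thickness but leaves ablation depth. Assume an ablation SD of 25 to 35 µm and a residual SD of 8 to 15 µm. The SD of change is then √(25² + 8²) = 26.2 µm to √(35² + 15²) = 38.1 µm. With 30 eyes per method the standard errors are 6.8 and 9.8 µm. A 10 µm shift at the larger SD gives about 17%, and a 16 µm shift at the smaller SD about 66%. Ablation depth therefore has to be in the model when the outcome is total or stromal thickness.

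**Precision.** Adjusting for a covariate with correlation r leaves a fraction 1 − r² of the variance. For r = 0.5, 0.7, 0.8 and 0.9 that is 75%, 51%, 36% and 19%. For an assumed 0.5 SD difference at 80% power and two-sided 5%, the eyes needed per method fall from 63 to 48, 33, 23 and 12. This gain applies even if the groups are balanced.

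**The case against.** A reader might infer that the protocol compares the methods by T-test, without randomisation and without adjustment, so that the comparison is confounded and imprecise. The document does not support this, for four reasons.

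- **The T-test is not assigned to Aim A.** It could be a paired before-and-after test, or could compare other groups. Linear regression is also listed and could carry a flap-method indicator with covariates. Covariate lists are commonly left to a statistical analysis plan, and none was available here.
- **Silence on assignment does not prove that it was not random.** If the method follows usual care, this is an ordinary observational imaging study; the protocol nowhere claims a randomised flap comparison.
- **The outcome of Aim A is not named.** The thickness identity describes total or stromal thickness. It does not describe flap thickness, an obvious candidate given section 2.2, and ablation depth bears less plainly on that.
- **Every magnitude is assumed.** The inflated error rates follow entirely from the imbalance put in; with none, the rate is 5%.

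All four stand, and they limit the point to a risk. They do not fill the gap in assignment, which is a design matter. Nor do they supply the ablation depth data that section 1.3 calls for.

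**Conclusion.** The point holds in a limited form. The protocol does not say how flap method is assigned, does not say which listed method serves Aim A, and does not list ablation depth as collected although its own hypothesis uses it. If the comparison were made by an unadjusted T-test and the method were not randomised, a difference in total or stromal thickness could not be attributed to the flap.

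The size of any bias cannot be derived from the protocol. The illustrative error rates (8.6% to 43.2% in standardised units, 13.8% to 28.0% on the micrometre assumptions) show only that modest imbalances would matter. They should not be quoted as properties of this study, and the micrometre figures do not carry over to flap thickness.

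The case for changing the text does not depend on those figures. The adjusted analysis uses a pre-operative scan already taken and a regression already listed. It is less exposed to bias from the measured covariates and is generally more precise. It does not remove confounding by factors that are not measured, which is why the wording of the conclusion matters too.

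**What to change.** 1. In section 3.6, name for Aim A a linear regression of the post-operative outcome at each visit on flap method, adjusted for the pre-operative thickness of the same layer. When the outcome is flap thickness, which has no pre-operative counterpart, adjust for pre-operative central corneal thickness and curvature. When the outcome is total or stromal thickness, also adjust for ablation depth.
2. Add ablation depth, copied from the laser record, to the data collected.
3. In section 3.5, state how flap method is assigned. If it is not randomised, describe Aim A in section 1.2 as an observational, adjusted comparison.

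Randomising the flap method is not suggested. It would change the surgery patients receive and goes well beyond a change of analysis wording.

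Cost: a few sentences, one extra data field, and a conclusion worded as an adjusted association if assignment is not random.

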**1.3** **Hypothesis**

During the observation of following-ups, OCT images might capture the changes before and after LASIK. The relationship between flap creation methods, ablation depth and corneal thickness might be captured. After LASIK, cornea edema might appear on the OCT images. As the longer observation time after surgery, cornea edema might reduce. Slit lamp will be used during following-ups and assist to image cornea. OCT will image the interfaces and boundaries of corneal sublayers and flaps.

At the same time, clinical exam results will be documented. Combined with OCT images, correlation between refractive regression, corneal curvature and corneal edema will be studied.

Keratoconus patients will be examed by clinical instruments. Patients of different stages will be included. OCT images will analysis combined with clinical data to study the relationship between the corneal thickness and disease courses.

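### The planned correlation of refractive regression, corneal curvature and edema names no adjustment for attempted correction, so an across-eye result could reflect only their shared dependence on it

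*Protocol*

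**What the plan says.** Section 1.3 of the protocol states that "correlation between refractive regression, corneal curvature and corneal edema will be studied", using the clinical examinations together with the OCT images.

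Section 3.6 is the whole analysis section. It lists the t-test and, as one further item, "Liner Regression, Pearson’s correlation". It assigns neither association method to a particular question. It mentions no covariate, partial correlation or stratification.

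Section 3.2.1 admits spheres from -1.00 to -12.00 D to the refractive surgery group. Section 3.3.1 includes subjective refraction among the pre-operative examinations, so a spherical equivalent can be derived for each eye.

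Section 1.3 does mention ablation depth and flap method, but for another outcome: "The relationship between flap creation methods, ablation depth and corneal thickness might be captured". Section 3.3.2 uses a random number table to "select one eye" for OCT, so fellow-eye clustering does not add to this point.

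**The concern.** The admitted range of myopia is wide, so attempted correction will differ greatly between eyes. Myopic LASIK works by changing corneal curvature, so postoperative curvature, or its change from before surgery, depends on how much correction was attempted. Edema and refractive regression may plausibly depend on it too. Flap method is a second candidate common cause. The protocol itself expects ablation depth and flap method to relate to corneal thickness, but names neither for this correlation.

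If two of the measures both vary with attempted correction, they will correlate across eyes even if neither has anything to do with the other at a given correction. Pearson's r cannot distinguish the two situations. A simple linear regression of one measure on the other cannot either, because it tests the same null hypothesis as Pearson's r. A significant result could then be taken to mean that edema or curvature accounts for refractive regression, when it shows only that higher myopes have more of each. The variable needed to tell these apart is already collected.

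**Working it through.** **No figure to reproduce.** The protocol states no sample size, alpha, power or target correlation. The check therefore runs over a range of assumed values.

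**Inputs**
- From section 3.2.1: sphere magnitude 1 to 12 D. If it is uniform over that range (an assumption), the SD is (12 - 1)/√12 = 3.18 D.
- Assumed: a and b, the correlations of two measures with attempted correction, each from 0 to 0.7.
- Assumed: n = 30, 50 or 100 eyes, one per subject, and a two-sided 5% test.

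**Step 1: correlation from the shared dependence alone.** The partial correlation of x and y given attempted correction is

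(r − ab) / √[(1 − a²)(1 − b²)].

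Setting this to zero gives r = ab. So 0.3 × 0.3 = 0.09, 0.5 × 0.5 = 0.25 and 0.7 × 0.7 = 0.49. If a or b is 0, r = 0.

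**Step 2: chance that plain Pearson gives p<0.05.** By Fisher's z, the test statistic is centred at atanh(r) × √(n − 3). For r = 0.25 and n = 50, this is 0.2554 × 6.856 = 1.751. The chance of exceeding 1.96 is 1 − Φ(0.209) = 0.417.

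**Step 3: simulation.** 4,000 runs per scenario, with correction uniform on 1 to 12 D and no link between x and y beyond it:

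| a, b | r = ab | Raw Pearson p<0.05, n = 30 / 50 / 100 | Partial correlation p<0.05, n = 30 / 50 / 100 |
|---|---|---|---|
| either is 0 | 0 | 5% / 5% / 5% (Fisher z) | not simulated |
| 0.3, 0.3 | 0.09 | 7% / 10% / 14% | 5.0% / 5.2% / 5.2% |
| 0.3, 0.5 | 0.15 | 12% / 17% / 32% | 5.4% / 4.9% / 4.9% |
| 0.5, 0.5 | 0.25 | 28% / 42% / 73% | 5.6% / 5.3% / 4.5% |
| 0.5, 0.7 | 0.35 | 50% / 74% / 95% | 5.0% / 4.9% / 4.5% |
| 0.7, 0.7 | 0.49 | 84% / 97% / 100% | 4.7% / 4.6% / 5.2% |

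Conditioning on attempted correction holds the rate at 4.5% to 5.6% in every simulated scenario. The simulation adjusts for attempted correction itself. Pre-operative spherical equivalent is a close stand-in for it, but not identical.

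**The case against.** A reader might infer that the protocol commits to an unadjusted Pearson correlation here. It does not. Section 3.6 lists linear regression in the same item and ties neither method to this question, so an adjusted analysis is not ruled out. Covariates for a secondary association are often left to a statistical analysis plan, which may exist and is not shown. Pooling of the two flap methods in one correlation is likewise not stated. These limits stand. What remains is that the protocol states the question, offers only these association methods, names no adjustment and admits a wide range of the likely common cause.

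The protocol also does not say that the correlation is taken across eyes. Section 1.3 speaks of follow-up, with edema falling over time. If each eye's own course over the visits were analysed, attempted correction would be constant within the eye and could not act in this way. The point is therefore limited to across-eye analyses.

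The raw correlation is, moreover, a valid description. In the scenarios above the marginal r really is ab, and a significant result is an error only if it is read as a link apart from attempted correction. The protocol does not state that reading, and this correlation is not among the Aims in section 1.2. That limits the weight of the point. It does not make an unadjusted r informative about how the measures relate at a given correction.

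Finally, pre-to-post curvature change is close to the correction achieved. Entering it beside pre-operative refraction would put two near-collinear terms in one model. This is right, and the fix is shaped accordingly.

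**Conclusion.** The concern holds in a limited form. As written, the plan names no way to separate a link among refractive regression, curvature and edema from their shared dependence on attempted correction, if the analysis is across eyes.

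The size is unknown. With a and b each from 0 to 0.7, the correlation produced by the shared dependence is 0 to 0.49, and the chance of p<0.05 with 50 eyes is about 5% to 97%. If either measure is unrelated to attempted correction there is no inflation. The values of a, b and n, the uniform spread of correction and the 5% test are all assumptions. No single row of the table should be quoted as this study's error rate.

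It is also tempting to say that attempted correction drives all three measures. The documents do not establish that. For curvature it follows from how the surgery works; for edema and refractive regression it is only plausible. The adjustment is still worth making, because the investigators cannot know beforehand that the dependence is weak, and an unadjusted r will not show whether it is.

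**What to change.** Add to section 3.6, for analyses across eyes:

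- Report the association of refractive regression with edema as a partial correlation, or as a linear-regression slope with its 95% CI, adjusted for pre-operative spherical equivalent and flap method. Keep the raw Pearson r as descriptive.
- Analyse curvature in a separate model. State whether it is the postoperative value or a change. Change over the postoperative visits is preferable, because the pre-to-post change is near-collinear with attempted correction.

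Spherical equivalent is the practical covariate because subjective refraction is already among the pre-operative examinations in section 3.3.1, whereas planned ablation depth is not listed there. Linear regression is already a named method.

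The cost is a few lines of text, two model degrees of freedom (one for spherical equivalent, one for the two-level flap method) and somewhat wider intervals. The adjusted association will probably be smaller than the raw one. No new data or visits are needed.

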**2 Study methods**

**2.1 Ultra-long scan depth OCT (UL-OCT)**

Custom-built OCT equippmented with superluminescent diode light source (SLD) with a wavelength centered at 830 nm and band width of 50 nm. The output power is less than 1.30 mW as safety limit (ANSI Z136.1). The scan depth is 7.8 mm in the air with scan speed of 24000 A-line/sec. The axial resolution was ~6.0μm and lateral resolution was ~15μm. This instrument capture images at horizontal and vertical directions. Real-time image in two directions might help to relocation on the corneal vertex. OCT probe was fixed on the slit lamp and easy to adjust the imaging capture positions.

UL-OCT is used to obtain 3 dimensional corneal images for corneal thickness.

**2.2 Ultra-high resolution OCT (UHR-OCT)**

Custom-built UHR-OCT equippmented with superluminescent diode light source (SLD) with a wavelength centered at 840 nm and band width of 100 nm. The output power is less than 1.30 mW as safety limit (ANSI Z136.1). The scan depth is 2.0 mm in the air with scan speed of 24000 A-line/sec. The axial resolution was ~3.0μm and lateral resolution was ~15μm. This instrument capture images at horizontal and vertical directions. Real-time image in two directions might help to relocation on the corneal vertex. OCT probe was fixed on the slit lamp and easy to adjust the imaging capture positions.

UHR-OCT is used to obtain 3 dimensional corneal images for corneal epithelium, Bowman’s layer and corneal flaps.

**2.3 Lab conditions**：dim light, temperature 1.5-25oC，humidity 30-50%.

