**3.2.1 Inclusion criteria**

Normal group：

1. no eye surgery,trauma; 2. no other eye dieases: glaucoma,retina disease; 3. no limiting image quality diseases: severe dry eye, eyelid calculi, conjunctivitis and pterygium; 4. quit contact lens: RGP > 4 weeks, SCL > 2 week; 5. no fixing problem.

Refractive surgery group：

1. age：≥18yrs；2. refractive status：sphere：-1.00~-12.00 D, cylinder：≤ -6.00 D；3. refractive status maintain stable in recent 2 yrs，progressive ≤ 0.50 D per year.

Keratoconus group：

Suspected and diagnosed Keratoconus patients ：1. history of myopia and astigmatism；2. corrected visual acuity <1.0；3. abnormal corneal topography：central anterior corneal curvature >47D, curvature difference of inferior 3mm and superior 3mm of anterior cornea IS>3D, binocular curvature difference >1D；4.slit lamp observe one of the signs：corneal stromal thinning, corneal cone, Fleischer’s ring, Vogt stria, cornea scar.

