**4. Notice：**

(1) Using apex to adjust cornea vertex registration and relocation;

(2) Keep iris plane balanced;

(3) Check the image quality after each acquisition. Reacquire if the image quality is not good enough.

(4) Open the eyelid wide to avoid eye lash artifacts.

(5) Check 3D scanning image quality. Require if the reconstruction is not smooth.

**B． UHR-OCT：**run: C:\OCT\combined_x-y\OCT-T34-Combined_1.vi

1. Obtain OCT images as following：

**1）Central horizontal 2D scanning：**calibrated scan width 8.425 mm. Scanning setting：“X/Y scan width” set as 7, “line rate” set as 24000 k/A-line，“scan pattern” set as 2048×326 mm.

[figure not shown]

**2）Nasal horizontal 2D scanning：**calibrated scan width 8.425 mm. Scanning setting as “1）Central horizontal 2D scanning”.

**3）Temporal horizontal 2D scanning:** calibrated scan width 8.425 mm. Scanning setting as “1）Central horizontal 2D scanning”.

**4）Central vertical 2D scanning：**calibrated scan width 8.418 mm. Scanning setting：“X/Y scan width” set as 7, “line rate” set as 24000 k/A-line，“scan pattern” set as 2048×326 mm.

[figure not shown]

**5）Superior vertical 2D scanning：**calibrated scan width 8.418 mm. Scanning setting as “1）Central vertical 2D scanning”.

**6）Inferior vertical 2D scanning：**calibrated scan width 8.418 mm. Scanning setting as “1）Central vertical 2D scanning”.

**7）Central 3D radial scanning：**calibrated scan width 8.418 mm. Scanning setting：“X/Y scan width” set as 10.5, “line rate” set as 24000 k/A-line，“scan pattern” set as 2048×324 mm radial.

[figure not shown]

**2. Naming rules：** NO1_XX_S_1M_OD_N_2D_X10_1

**3. Data saving:**  E:\LASIK_OCT\UHR\Time\Subject

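### The UHR-OCT 3D radial scan pairs setting 10.5 with a width that belongs to setting 7; if 10.5 is what is entered, the outer map leaves the 2.0 mm depth range and its lateral scale is off by about 1.5

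*Protocol*

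**What the plan says.** Protocol section 2.2 gives the UHR-OCT its depth range: "The scan depth is 2.0 mm in the air with scan speed of 24000 A-line/sec". It also gives its purpose: "UHR-OCT is used to obtain 3 dimensional corneal images for corneal epithelium, Bowman’s layer and corneal flaps". Section 2.1 assigns 3D corneal thickness to the other instrument, the UL-OCT, which has 7.8 mm of depth.

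Section 3.3.2, part B, lists the UHR-OCT scans:

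- Central horizontal 2D: "calibrated scan width 8.425 mm. Scanning setting：“X/Y scan width” set as 7".
- Central vertical 2D: "calibrated scan width 8.418 mm. Scanning setting：“X/Y scan width” set as 7".
- Central 3D radial (scan 7): "calibrated scan width 8.418 mm. Scanning setting：“X/Y scan width” set as 10.5".

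Part A gives the UL-OCT scans in the same form, for example "calibrated scan width 18.291mm.Scanning setting：“X/Y scan width” set as 15" for the 3D radial scan and "calibrated scan width 12.139 mm. Scanning setting：“X/Y scan width” set as 10" for the horizontal 2D scan.

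Section 3.4 has automated software deliver the thickness of each sublayer from UHR-OCT, and automated code deliver results for all layers. The protocol states no diameter over which sublayers are read. Its only corneal curvature figure is the keratoconus criterion in section 3.2.1, "central anterior corneal curvature >47D".

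**The concern.** The 3D radial scan carries two numbers that do not agree on the protocol's own scale. An operator who follows the text enters 10.5. If the scanner responds as it does for every other listed scan, the sweep is about 12.6 mm, not 8.418 mm. This has two consequences.

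First, the cornea is curved and the UHR-OCT sees only 2.0 mm of depth. On a wide enough sweep the periphery falls below the window, and software may miss the layers there or place false boundaries. The in-range diameter shrinks as the cornea steepens. An average over whatever is visible would therefore cover a different area in steep keratoconus eyes than in normal eyes, and before than after surgery.

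Second, a map scaled to 8.418 mm but swept over 12.6 mm puts each reading at the wrong distance from the centre.

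Sections 1.2 and 1.3 plan comparisons across visits, flap methods and keratoconus stages, so the area and location of each reading should be the same in every eye.

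**Working it through.** **Step 1: reproduce the stated width.** Ratio = calibrated width / setting, all from section 3.3.2.

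| Scan | Setting | Width (mm) | mm per unit |
|---|---|---|---|
| UL 3D radial | 15 | 18.291 | 1.219 |
| UL horizontal 2D | 10 | 12.139 | 1.214 |
| UL vertical 2D | 10 | 12.248 | 1.225 |
| UHR horizontal 2D | 7 | 8.425 | 1.204 |
| UHR vertical 2D | 7 | 8.418 | 1.203 |
| UHR 3D radial | 10.5 | 8.418 | **0.802** |

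The stated 8.418 mm is not reproduced from 10.5. On the UHR vertical ratio, 10.5 × 8.418/7 = 12.63 mm; over all five other ratios the result is 12.63 to 12.86 mm. The lateral discrepancy is 12.63/8.418 = 1.5. A reading plotted 3 mm from the centre would come from 4.5 mm.

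**Step 2: depth needed.** Assumptions not in the protocol:

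- Keratometric index 1.3375, so R = 337.5/K: 7.79 mm at 43.3 D, 7.18 mm at 47 D, 6.14 mm at 55 D.
- Asphericity Q of 0 or −0.25.
- Tissue index 1.38.
- A flat scan field, with the apex at the very top of the window (the most favourable placement).
- Anterior layers including flap up to 0.20 mm, or 0.20 × 1.38 = 0.28 mm optically.
- Full cornea 0.55 mm, or 0.55 × 1.38 = 0.76 mm optically.

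Front-surface drop at half-width h: sag = h² / (R + √(R² − (1+Q)h²)).

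*If the sweep is 12.63 mm (h = 6.31 mm):*

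- 43.3 D: 3.2 mm (Q = 0), 3.0 mm (Q = −0.25).
- 47 D: 3.8 mm (Q = 0), 3.4 mm (Q = −0.25).

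Each exceeds 2.0 mm before any tissue is added. Widening the assumptions to R = 7.18 to 8.6 mm and Q = 0 to −0.5 gives 2.5 to 3.8 mm. A spherical cornea would need R = (6.31² + 2.0²)/(2 × 2.0), about 11.0 mm, for its front surface to stay in range.

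*If the sweep is the stated 8.418 mm (h = 4.21 mm), Q = 0:*

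| Curvature | Sag | Plus anterior layers | Plus full cornea |
|---|---|---|---|
| 43.3 D | 1.23 | 1.51 | 1.99 |
| 47 D | 1.36 | 1.64 | 2.12 |
| 55 D | 1.67 | 1.95 | 2.43 |

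The anterior layers fit in all three. The full cornea is at the limit at 43.3 D and past it at 47 D and above, at the edge only.

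**Step 3: diameter that stays in range.** With Q = 0, diameter = 2√(2RS − S²), where S is 2.0 mm minus the optical thickness.

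- Anterior layers (S = 1.72): 9.8 mm at 43.3 D, 9.3 mm at 47 D, 8.5 mm at 55 D.
- Full cornea (S = 1.24): 8.4, 8.1 and 7.4 mm.

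Any lower placement of the apex in the window makes these smaller.

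**The case against.** The strongest objection is that the protocol states 8.418 mm for this very scan. At that width the layers section 2.2 assigns to the UHR-OCT fit within 2.0 mm to the edge, even at 55 D on the assumptions above. The document does not show which number is wrong: 10.5 may be a misprint for 7, or this mode may have its own calibration. This objection stands, so the depth problem is conditional on the setting.

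There are signs in favour of 10.5. The UL-OCT 3D scan uses 15 against 10 for 2D, a ratio of 1.5, and 10.5/7 is also 1.5. The UL radial scan keeps the usual scale (1.219), so radial mode does not by itself shrink the sweep. The figure 8.418 matches the vertical 2D entry to three decimals, as a copied label would. This is inference, not proof.

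It is also fair to say that full thickness in 3D already belongs to the UL-OCT, that section 3.4 does not require layers to be read to the scan edge, and that the protocol names no endpoint in the outer ring. Analysis zones may be set in a statistical analysis plan that is not at hand. Image-quality checks with repeat acquisition, and manual boundary measurement, give some protection against false boundaries, but repeating a scan cannot extend a depth range.

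**Conclusion.** The document shows a mismatch between setting and calibrated width for one scan, by a factor of 1.5. The rest is conditional. If 10.5 is entered and the scanner follows its usual scale, the anterior layers go out of range beyond about 9 to 10 mm in 43 to 47 D eyes, and sooner in steeper ones, and a lateral scale based on 8.418 mm is wrong by about 1.5. If 8.418 mm is the true width, neither problem arises for epithelium, Bowman's layer and flap; only the posterior surface of steep eyes is marginal, at the edge.

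A reader might infer that the UHR-OCT cannot measure these layers over the outer map, or that some two fifths of the map is lost: 1 − (9.8/12.63)² = 40% at 43.3 D and 1 − (9.3/12.63)² = 46% at 47 D. The protocol does not support that as an unconditional claim. It disregards the stated 8.418 mm and supposes that the cornea fills a 12.6 mm circle. Nor does the protocol show a biased result, since no stated analysis uses the outer ring.

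The depth figures rest on assumed radius, asphericity, refractive index, layer thickness and a flat field. The mismatch itself rests only on the protocol's numbers.

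**What to change.** In section 3.3.2, part B, scan 7, reconcile the setting with the calibrated width. Use a setting whose calibrated width fits the 2.0 mm depth; setting 7, which on the vertical 2D scan gives the stated 8.418 mm, is one choice. If maps have already been acquired at 10.5, confirm the true sweep and rescale lateral positions before analysis.

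Add one sentence to section 3.4: UHR-OCT sublayers are read over one common central diameter, the same for all eyes and visits and within range for the steepest eyes (for example 6 to 7 mm, to be confirmed on the instrument), and automated boundaries outside it are discarded. Full thickness comes from the UL-OCT, as section 2.1 already provides.

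The cost is one scanner setting and one sentence. The small downside is no UHR 3D data in the far periphery, which the nasal, temporal, superior and inferior UHR 2D scans partly cover.
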